### Sample size estimation

Given the lack of existing data on the influence of anaesthesia type and form during TEE on swallowing in ischaemic stroke and TIA patients, this study is designed as a pilot trial. A total of 50 participants will be enrolled, with 25 patients in each group (stroke vs. TIA). The primary aim of this exploratory phase is to gather preliminary data to estimate effect sizes. These estimates will then serve as the basis for a formal power calculation and definitive sample size planning for a subsequent full-scale study.

### Recruitment

Before the trial onset, all clinical staff at the recruitment site will be provided with information about the trial to share and discuss with potential participants. Therefore, all patients admitted to the stroke unit at UKGM in Giessen will be screened for eligibility to participate in the trial. If this approach does not yield enough participants, study-related advertisements will be displayed to aid in recruitment.

### Assignment of interventions: allocation

Since this is not a randomized trial the participants will be assigned to the aforementioned groups according to the diagnosis. The allocation sequence will be sequentially numbered by the allocating investigator MD and stored in a secure database only accessible by this person. The trial investigator responsible for enrollment and allocation will provide patients’s enrollment sequence number and allocate participants to respective groups after viewing the diagnosis. All enrolled patients will receive the same interventions in both groups.

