#### TEE

The Department of Cardiology at the University Medical Centre of the Justus-Liebig-University in Giessen conducts the TEE using a Philips EPIC 7 C ultrasound workstation and Philips Type X7 and X8 probe. For the procedure, anaesthesia is administered either intravenously with propofol or as a combination of intravenous propofol and local pharyngeal anaesthesia using lidocaine spray. Patients are required to refrain oral intake of food and liquids for at least 6 h prior to the TEE. This restriction continues for 30 min and up to 1 h after the TEE to ensure and minimize complications of potential post TEE dysphagia.

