## Outcomes

### Primary outcome

The primary outcome will assess the impact of the type and form of anaesthesia (intravenous vs. local) administered during TEE on swallowing in patients with ischaemic stroke and TIA, based on the aforementioned dysphagia scores [30–34].

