### Definition of dysphagia

Dysphagia is determined with the following cut-off values of the dysphagia scores:

Secretion Severity Rating Scale for Saliva Management (SSRS): SSRS ≥ 1; Penetration Aspiration Scale (PAS): PAS ≥ 3; Yale Pharyngeal Residue Severity Rating Scale: YS ≥ 3; Functional Oral Intake Scale (FOIS-G): FOIS-G < 7. Differences in patient-related data between the two groups: dysphagia/non-dysphagia group and intravenous vs. oral anaesthesia group are tested using Pearson’s chi-square test, Fischer’s exact test, *t*-test for independent samples or the Mann–Whitney *U*-test. For the purpose of logistic regression analyses, we intend to apply a median split to dichotomize the SSRS, PAS, YS and FOIS-G scores and create a binary outcome variable.

Assumptions for a *t*-test for independent samples are tested with the Levent test for variance homogeneity and the Shapiro–Wilk test including visual inspection of thedistribution plots for the assessment of normal distribution. If there is no homogeneity of variance or normal distribution, the Mann–Whitney *U* test for group differences is used. Correlations are calculated using the Pearson product-moment correlation or the Spearman rank correlation.

The inter-rater reliability between two raters is determined using a linearly weighted Cohen’s kappa, as this takes into account matches that could have arisen by chance on the one hand and places more weight on high non-matches on the other [39]. Furthermore, the percentage agreement and the Spearman rank correlation are specified for the agreement between two raters. In the case of a calculation of inter-rater reliability with more than two raters, a general agreement of all raters including subtraction of agreements by chance is calculated using Fleiss kappa [39].

Effect sizes are given according to Cohen’s d with a 95% confidence interval. *p*-values are given for all statistical results. The criterion for statistical significance is set at *p* < 0.05. Conclusions about clinically, practically and scientifically relevant correlations or differences are not made solely on the basis of the defined statistical significance [40].

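### The primary anaesthesia contrast is not tied to diagnosis or baseline swallowing, so its effect size can partly reflect stroke/TIA case mix

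*Protocol article*

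**What the plan says.** Under Primary outcome: "The primary outcome will assess the impact of the type and form of anaesthesia (intravenous vs. local) administered during TEE on swallowing". Under TEE, the exposure arises in routine care: "anaesthesia is administered either intravenously with propofol or as a combination of intravenous propofol and local pharyngeal anaesthesia using lidocaine spray". No section says which patients receive which regimen.

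The controlled grouping is a different one. Eligibility criteria and Sample size estimation fix 25 stroke and 25 TIA patients, and under Assignment of interventions: allocation, "Since this is not a randomized trial the participants will be assigned to the aforementioned groups according to the diagnosis". The same section adds: "All enrolled patients will receive the same interventions in both groups".

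For analysis, the section Definition of dysphagia says that differences in patient-related data between groups, among them "dysphagia/non-dysphagia group and intravenous vs. oral anaesthesia group are tested using" chi-square, Fisher, t or Mann–Whitney tests. Effect sizes are given as Cohen's d. A regression is also planned: "For the purpose of logistic regression analyses, we intend to apply a median split to dichotomize the SSRS, PAS, YS and FOIS-G scores". No covariates are named for it.

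Baseline NIHSS and a FEES before TEE (FEES 1) are collected (Table 1; Data collection and management). Sample size estimation says the estimated effect sizes will be used to plan a full-scale study.

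**The concern.** Fixing 25 and 25 by diagnosis does not balance diagnosis within the two anaesthesia regimens. If the choice of regimen follows diagnosis, or something that goes with it, one regimen group will contain more stroke patients than the other. If stroke patients also swallow worse than TIA patients whatever anaesthesia they had, an unadjusted contrast between regimens picks up that difference. Comparing patient characteristics between regimen groups would reveal the imbalance but would not remove it.

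At stake is the pilot's main product. Its stated purpose is to supply effect sizes for a definitive sample size, and the Discussion aims to find which factors lead to dysphagic symptoms after TEE. A case-mix difference read as an anaesthesia effect would mislead on both.

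**Working it through.** **1. The plan's own figure.** 25 + 25 = 50 agrees with the stated total. No effect size, standard deviation or power is given, so there is nothing further to reproduce.

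**2. Inputs.**
- Dysphagia in stroke, pS = 0.50 (Background, which says at least 50%).
- Dysphagia in TIA, pT = 0.10: my assumption, range 0.05 to 0.15.
- Share of stroke patients given spray, f, with 1 − f of TIA patients: my assumption, 0.6 to 0.8.
- True anaesthesia effect: zero.
- The contrast is taken as propofol alone versus propofol plus spray, as under TEE.

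**3. Pooled rates.** With equal cohorts:
- Spray group: f·pS + (1 − f)·pT
- Other group: (1 − f)·pS + f·pT
- False difference: (2f − 1)(pS − pT)

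| Spray in stroke / TIA | Spray group | Other group | Difference | Odds ratio |
|---|---|---|---|---|
| 60% / 40% | 34% | 26% | 8 points | 1.5 |
| 70% / 30% | 38% | 22% | 16 points | 2.2 |
| 80% / 20% | 42% | 18% | 24 points | 3.3 |

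At 70%/30% the difference is 0.4 × (0.50 − pT): 18 points for pT = 0.05 and 14 points for pT = 0.15. It is zero if f = 0.5 or pS = pT. If spray is commoner in TIA, the sign reverses.

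**4. Chance of a false finding.** 20,000 simulated trials per scenario, whole patients, pT = 0.10, level 0.05 (two-sided assumed, since the protocol does not say). The runs put spray more often in TIA. In the three unequal splits both regimen groups have 25 patients, so swapping the labels leaves the rejection rates unchanged.

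| One regimen: stroke / TIA patients | Chi-square | Fisher | Mantel–Haenszel by diagnosis |
|---|---|---|---|
| 12 / 12 | 3.4% | 1.9% | 4.6% |
| 15 / 10 | 7.5% | 3.2% | 4.8% |
| 17 / 8 | 18% | 10% | 5.0% |
| 20 / 5 | 48% | 33% | 5.0% |

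Stratifying by diagnosis restores the nominal level. If regimen and diagnosis coincide completely (25 / 0), chi-square rejects in 91% of trials and no stratified estimate exists.

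**5. On the Cohen's d scale.** With an assumed stroke–TIA difference of d = 0.8 and no anaesthesia effect, the spurious d has size 0.15, 0.27 and 0.46 for the 15/10, 17/8 and 20/5 splits. With d = 0.5 it is 0.10, 0.18 and 0.29.

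**6. Precision cost of stratifying.** Assume equal residual variance and compare with a pooled 25 versus 25 contrast, whose standard error is proportional to √(2/25) = 0.283.
- 17/8 split: each cohort alone gives √(1/17 + 1/8) = 0.429, a ratio of 1.52. The average of the two cohorts gives 0.429/√2 = 0.303, a ratio of 1.07.
- 20/5 split: √(1/20 + 1/5) = 0.500, a ratio of 1.77. The average gives 0.354, a ratio of 1.25.

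**The case against.** The case on the other side is substantial.

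- **The test sentence.** A reader might infer that the protocol fixes unadjusted tests of the swallowing scores between regimens. It does not clearly do so: the sentence concerns patient-related data, and the list of such data under Statistical methods contains diagnosis and TEE duration but no swallowing score. This stands. What remains is that no other method is spelled out for regimen groups.
- **The regression.** A reader might take logistic regression to be mentioned only as a way of producing a binary outcome. The text runs the other way: the median split serves a planned regression. Covariate lists are often left to an analysis plan, so their absence alone is no fault.
- **Pooling.** The Objectives speak of swallowing in both cohorts, which suggests a within-diagnosis reading. The statistical text does not carry it out, but neither does it say that the cohorts will be pooled.
- **Same interventions.** This might be read as a flat contradiction of the two regimens. Table 1 lists only FEES and TEE under interventions, and on that reading the sentence is true. It is ambiguous rather than shown to be wrong.
- **Size.** The TIA rate and the regimen split are assumed, and no section suggests that regimen follows diagnosis. The 50% is a general stroke figure; the exclusions (aphasia, lack of alertness, dementia and others) may lower it among those enrolled. The illustration uses prevalence after TEE, whereas FEES 1 allows change to be examined.
- **Status.** This is an openly non-randomised, exploratory pilot, and the protocol says conclusions will not rest on significance alone. That lowers the severity. It does not protect the effect size, which is what the pilot exists to estimate.

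**Conclusion.** The point holds in a limited form. The primary contrast is between regimens that the design neither assigns nor balances, and the protocol does not tie the estimate to diagnosis or to pre-TEE swallowing. The documents therefore leave open an effect size that partly reflects stroke/TIA case mix. Under the stated assumptions (50% and 10% dysphagia, a 70%/30% split, no true effect) the false difference is 16 points, or 14 to 18 points over a TIA rate of 15% to 5%.

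A reader might go further and conclude that the comparison is biased, or that the study cannot answer its question. The documents do not support that: bias needs both associations, neither is shown, and if either is absent the bias is zero. This should be fixed, because the remedy uses data already collected, but it does not invalidate the pilot.

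**What to change.** 1. Under Primary outcome and in the statistical text, state that the anaesthesia contrast is estimated within, or stratified by, diagnosis cohort and adjusted for the pre-TEE FEES 1 score, with NIHSS as a further covariate where numbers allow. Say whether the planned logistic regression is the model that does this.
2. Report the result as an association.
3. Cross-tabulate regimen by cohort. The quarterly group meetings already planned could follow this table during recruitment. State that no anaesthesia conclusion will be drawn from a cohort in which nearly all patients had one regimen.
4. Under Assignment of interventions: allocation, reconcile the sentence on same interventions with the two regimens described under TEE. If it refers to FEES and TEE, as Table 1 suggests, and not to the anaesthesia regimen, say so.

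The cost is protocol wording and one table. The interval will be wider with 25 patients per cohort: in the splits worked above, the standard error is 1.07 to 1.25 times larger for the stratified estimate and 1.52 to 1.77 times larger within a single cohort. The causal claim becomes weaker. Adjustment handles diagnosis and measured baseline values only; unrecorded reasons for choosing a regimen remain.

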### Blinding

This is a single-blinded trial. All evaluators of FEES intervention and the statisticians will be blinded for the allocation to the groups respectively the diagnosis of participants. For the unbiased evaluation of the FEES procedure, the FEES video sequences and all trial outcomes will be randomized and pseudonymized by an independent examiner. They will then be presented to a neurology specialist and an SLT, each with at least 5 years of experience treating stroke patients and certified in FEES by the German Society of Neurology and the European Society for Swallowing Disorders. Both the neurology specialist and the SLT will be blinded to group allocation and all previous results, and they will assign SSRS, PAS, YS and FOIS-G scores to all consistencies applied in the swallowing evaluation.

### Procedure for unblinding if needed

Unblinding is limited to critical situations, such as serious adverse events or life-threatening conditions requiring knowledge of the treatment for proper medical care. The decision to unblind must involve the PI with proper documentation of the justification and approval. In case of unbliding treatment, assignments will be accessed only when authorized by the PI. The unblinding procedure will comprise the verification of the participant’s identity and retrieving the allocation details by accessing a secure database. The information then will be shared with the medical team handling the participant. The full event will be recorded and documented comprising key details (participant ID, date, time, reason for unblinding and personnel involved). These records will be kept as part of the trial documentation. In order to limit the impact of unblinding on the study the unblinding will be restricted to the specific participant involved, ensuring no other participants, study staff or researchers are exposed to the allocation information. If required, ethics committee and any regulatory authorities will be informed Table 1.

**Table 1 Tab1:** Participant timeline

**Interventions**		**Timepoint**				
		***Baseline***	***T1***	***Within 3–5 d after admission***	***T2***	***T3***
***Routine treatment***	Admission to stroke unit	x				
	NIHSS score	x				
	MRS score	x				
	BI score	x				
	CCT	x				
	Routine stroke treatment	x				
	Dysphagia assessment/FEES (if necessary)	x				
***Enrollment***	Inclusion/exclusion criteria	x				
	Informed consent	x				
	Group allocation according to diagnosis	x				
***Interventions***	FEES 1		x			
	TEE			x		
	FEES 2				x	
	FEES 3					x

### Data collection and management

We will collect demographic information at baseline from the digital patient file. Symptom evaluation of stroke or TIA will be conducted by a neurological MD. Evaluation of cCT will be performed and documented by a neuroradiologist within the routine work-up of stroke. Within the routine stroke treatment stroke relevant scores National Institutes of Health Stroke Scale (NIHSS), Modified Rankin Scale (MRS) and Barthel Index (BI) will be documented. NIHSS is a 15-item assessment tool designed to evaluate stroke severity. According to the latest guidelines from the National Stroke Foundation, it is endorsed as a reliable instrument for assessing stroke severity in emergency department settings [35]. MRS is a clinician-reported tool that assesses global disability on a 7-point scale, ranging from no symptoms and perfect health to death. It is the most commonly used outcome measure in acute stroke trials [36]. BI is a ten-item scale used to assess the ability to perform activities of daily living (ADLs), including tasks like feeding, bathing, managing continence, mobility and dressing. It has been shown to have strong internal consistency and validity when evaluating functional status in elderly patients after cerebrovascular events [37]. Swallowing assessment within 24 h after admission to the stroke unit is conducted by an SLT. The 70-ml water swallow test is administred to define aspirations risk [38]. FEES is conducted prior to enrollment to the trial if the swallowing assessment confirms aspiration risk and is needed to provide adaqute dysphagia management and diet recommendations. Upon the enrollment in the trial following dysphagia relevant FEES scores are documented: SSRS, PAS, YS and FOIS-G [30–33].

### Plans to promote participant retention and complete follow-up

N/a. All patients will receive the planned interventions within the routine stroke treatment according to the guidelines of the German Society of Neurology.

### Patient public involvement

No patient public involvement has been planned for this trial.

### Data management

Before starting participant enrollment, research staff will receive thorough training on how to complete case report forms (CRFs) and how to retrieve relevant information from the digital patient file. Thus, the procedural guidelines specified in the protocol are clarified with the goal of improving the consistency and reliability of the data. Throughout the trial, all data records and report will be accurately checked for completeness. Treatment changes, medications, withdrawals and missed assessment will be verified and recorded for every participant. The CRF will be thoroughly reviewed at the end of trial enrollment in order to correct all errors or omissions. Any necessary changes or comments will be signed and dated by the PI. Any issues discovered from discrepancies will be promptly resolved, either through additional data, corrections or clarifications from the PI. A data manager will perform a second review of the checked CRFs to identify any potential issues that may have been missed. This process will help with further corrections or additions as needed.

### Confidentiality

Trial participants will receive a unique code upon enrollment in the trial. The statisticians and the evaluating team will only have access to the patient code. No disclosure of real patient information will be available. All personal participants’ details will be stored in a secured database and accessible only to authorized members of the research team.

### Statistical methods

Patient-related data such as age, gender, diagnosis, relevant medication, TEE duration and application form of anaesthesia (local or intravenous) are evaluated descriptively with frequency data, mean values with standard deviations or medians with interquartile ranges.

### Definition of dysphagia

Dysphagia is determined with the following cut-off values of the dysphagia scores:

Secretion Severity Rating Scale for Saliva Management (SSRS): SSRS ≥ 1; Penetration Aspiration Scale (PAS): PAS ≥ 3; Yale Pharyngeal Residue Severity Rating Scale: YS ≥ 3; Functional Oral Intake Scale (FOIS-G): FOIS-G < 7. Differences in patient-related data between the two groups: dysphagia/non-dysphagia group and intravenous vs. oral anaesthesia group are tested using Pearson’s chi-square test, Fischer’s exact test, *t*-test for independent samples or the Mann–Whitney *U*-test. For the purpose of logistic regression analyses, we intend to apply a median split to dichotomize the SSRS, PAS, YS and FOIS-G scores and create a binary outcome variable.

Assumptions for a *t*-test for independent samples are tested with the Levent test for variance homogeneity and the Shapiro–Wilk test including visual inspection of thedistribution plots for the assessment of normal distribution. If there is no homogeneity of variance or normal distribution, the Mann–Whitney *U* test for group differences is used. Correlations are calculated using the Pearson product-moment correlation or the Spearman rank correlation.

The inter-rater reliability between two raters is determined using a linearly weighted Cohen’s kappa, as this takes into account matches that could have arisen by chance on the one hand and places more weight on high non-matches on the other [39]. Furthermore, the percentage agreement and the Spearman rank correlation are specified for the agreement between two raters. In the case of a calculation of inter-rater reliability with more than two raters, a general agreement of all raters including subtraction of agreements by chance is calculated using Fleiss kappa [39].

Effect sizes are given according to Cohen’s d with a 95% confidence interval. *p*-values are given for all statistical results. The criterion for statistical significance is set at *p* < 0.05. Conclusions about clinically, practically and scientifically relevant correlations or differences are not made solely on the basis of the defined statistical significance [40].

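### Read literally, the anaesthesia effect on swallowing is analysed only through dichotomised scores, and the pilot's effect size is not defined on the graded scales

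*Protocol article*

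**What the plan says.** Primary outcome: "The primary outcome will assess the impact of the type and form of anaesthesia (intravenous vs. local) administered during TEE on swallowing", and this is "based on the aforementioned dysphagia scores". Those scores are graded: SSRS has 4 points, PAS 8, the Yale scale 5 and FOIS-G 7 (section on dysphagia severity assessment).

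Statistical methods: "Patient-related data such as age, gender, diagnosis, relevant medication, TEE duration and application form of anaesthesia (local or intravenous) are evaluated descriptively".

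Definition of dysphagia: cut-offs on the four scales define dysphagia (for example PAS of 3 or more). The group comparison follows: "Differences in patient-related data between the two groups: dysphagia/non-dysphagia group and intravenous vs. oral anaesthesia group are tested using" chi-square, Fisher, t or Mann–Whitney tests. For logistic regression the plan is to "apply a median split to dichotomize the SSRS, PAS, YS and FOIS-G scores and create a binary outcome variable"; no predictor is named. Later in the same section: "Effect sizes are given according to Cohen’s d with a 95% confidence interval".

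Sample size estimation: "The primary aim of this exploratory phase is to gather preliminary data to estimate effect sizes". These estimates are to feed the power calculation of a full-scale study.

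**The concern.** The sentence that assigns tests to the anaesthesia groups names patient-related data as the variable under test. The swallowing scores, which are the primary endpoint, are not named there. Where the plan does say how the scores are used in a way that could address anaesthesia, it first cuts them into two classes. The only effect size it names is attached to no variable.

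The pilot's product is an effect size for planning a larger trial. An analyst who follows the text literally would deliver tables of characteristics by regimen, a cross-tabulation of regimen against dysphagia status, and perhaps odds ratios on median-split scores. No estimate of how far the graded scores differ between regimens would have to appear. The median split adds a problem of its own: its cut point comes from this sample, so an odds ratio built on it does not carry over cleanly to a new sample with a different median.

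**Working it through.** **Step 1: where a swallowing score could meet the anaesthesia contrast.**

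| Place in the protocol | Variable analysed | Graded score by regimen? |
|---|---|---|
| Definition of dysphagia, tests by anaesthesia group | Patient-related data; no score among the examples in Statistical methods | Not stated |
| Definition of dysphagia, tests by dysphagia status | Patient-related data, which include the form of anaesthesia | No: swallowing is in two classes |
| Definition of dysphagia, logistic regression | Median-split SSRS, PAS, YS, FOIS-G | No: two classes, predictors unnamed |
| Definition of dysphagia, Cohen's d | Unspecified | Not stated |
| Secondary outcomes, correlations | TEE duration with FOIS-G deterioration and with examiner experience | No: another question |
| Secondary outcomes, interrater reliability | Scores between raters | No: another question |

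No row gives a stated comparison of graded scores between regimens. Two rows give a binary route to the primary question.

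**Step 2: the plan's own figure.** The total of 50 patients is not derived from a power calculation, so there is nothing to reproduce.

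**Step 3: what dichotomising costs, as an illustration.**

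From the protocol: N = 50, significance at 0.05, cut at PAS of 3 or more. Assumed, because the protocol gives no values: two-sided tests; PAS scores 1 to 8 under one regimen with probabilities 40/20/12/9/7/5/4/3%; proportional odds; odds ratio 4 or 2; regimen split 25/25 or 35/15.

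- P(PAS ≥ 3) under the reference regimen = 12 + 9 + 7 + 5 + 4 + 3 = 40%, so the odds are 0.40/0.60 = 0.667.
- Odds ratio 4: odds 2.667, probability 2.667/3.667 = 73%.
- Odds ratio 2: odds 1.333, probability 1.333/2.333 = 57%.

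Simulated power:

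| Odds ratio | Split | Mann–Whitney on PAS | Chi-square on PAS ≥ 3 | Difference (points) |
|---|---|---|---|---|
| 4 | 25/25 | 76% | 69% | 7 |
| 4 | 35/15 | 68% | 57% | 11 |
| 2 | 25/25 | 27% | 26% | 1 |
| 2 | 35/15 | 23% | 19% | 4 |

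Repeat runs move each difference by about a point. I therefore summarise the gain as about 6 to 11 points at odds ratio 4 and about 1 to 4 at odds ratio 2. With no effect, Mann–Whitney rejects in about 5% of runs and chi-square in about 6% at 25/25. A median split tested by chi-square performs much like the fixed cut (70% and 58% at odds ratio 4).

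Fisher's test reaches only 57% and 46% at odds ratio 4, which makes the loss look like 76 − 57 = 19 and 68 − 46 = 22 points. But it rejects in only about 3% of runs with no effect, so part of that gap is the test's conservatism and not dichotomisation.

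Treating the score as a continuous normal variable with an assumed d of 0.8 gives 81% for the graded score and 60% for a median split at 25/25. Scales of 4 to 8 points with many patients at the best score are not like that, so I do not rest the size on this model.

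**The case against.** The strongest reply is that the fault is one loose noun. The list of patient-related data is introduced as a set of examples, and it already reaches beyond patient characteristics to procedure data. The group-test sentence comes straight after the score cut-offs, names the anaesthesia groups and includes Mann–Whitney, which is also the stated fallback when normality or equal variance fails. With the primary outcome in mind, a reader can suppose that the scores were meant. This stands in part: the intention may well have been right. The text still does not say so, and its explicit instruction for the scores as an outcome is a median split.

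Three stronger readings are tempting, and the protocol does not support them.

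- That the primary question has no analysis at all. The form of anaesthesia is itself listed as patient-related data and can be tested against dysphagia status, and the logistic regression uses the scores in binary form.
- That significant differences in age or diagnosis between regimens would pass for an effect on swallowing. Nothing in the protocol suggests that such results would be read that way.
- That Cohen's d will be computed on the wrong variable. The sentence is general; it fails to say which variable, which is a gap and not an error.

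It is also fair to say that the protocol sets estimation as the aim and does not rest conclusions on significance alone, so power is secondary. That shifts the weight of the point to the undefined effect size. Finally, a condensed article may leave the mapping of tests to variables to a fuller plan. That would answer a plain omission. It does not answer a sentence that names another variable, or a stated median split.

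**Conclusion.** The point holds in a limited form. Taken literally, the plan reaches the effect of anaesthesia on swallowing only through dichotomised scores, and the effect size that the pilot is to hand on is not defined on the graded scales. The textual finding does not depend on the simulation; the open wording of the list means that it may be a drafting slip.

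The cost in power is modest: about 6 to 11 points at an odds ratio of 4 and about 1 to 4 at 2, measured against chi-square. These figures depend on the assumed PAS distribution, proportional odds and the assumed regimen splits. The larger consequence is for planning: without a stated graded-score estimate by regimen, the pilot may not yield the quantity on which the full-scale sample size is to rest.

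**What to change.** In the analysis text under Definition of dysphagia:

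1. Describe patient-related data by anaesthesia regimen.
2. Compare the post-TEE SSRS, PAS, Yale (valleculae and piriform sinus) and FOIS-G scores between regimens as ordinal scores, by Mann–Whitney or a proportional-odds model, each with an effect estimate and 95% confidence interval.
3. State that these are the effect sizes carried forward under Sample size estimation.
4. Drop the median split, and keep the cut-off dysphagia rate as a supportive result.

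The regimen groups also need one label. Primary outcome contrasts intravenous with local, Definition of dysphagia contrasts intravenous with oral, and the TEE section describes propofol alone or propofol plus lidocaine spray. These passages must be reconciled.

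The cost is a few sentences and a few more lines of analysis, with no new data. The small downside is that the lead result becomes a rank-based effect or a common odds ratio, which is less immediate to readers than a simple rate.
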